**Methods:**

In this international, prospective, multicenter, observational study, we aim to include 700 patients across seven European countries. Patients will monitor their disease course for a period of two years using an online home monitoring program (I-FILE), which includes home spirometry, pulse oximetry, and PROMs. Results will be directly sent to the hospital via the online application. Patients will be asked to perform daily home spirometry and pulse oximetry in the first three months, followed by once weekly measurements for a period of two years. PROMs will be completed in the online I-FILE application every six months, including the King’s brief Interstitial Lung Disease Health Status, The EuroQol five dimensions five-level, Visual Analogue Scales on cough, dyspnea, fatigue and general complaints, Leicester Cough Questionnaire, Fatigue Assessment Scale, Work Productivity and Activity Impairment Questionnaire, Global Rating of Change Scale, and Living with Pulmonary Fibrosis questionnaire.

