### Endpoints and statistical analysis

We will evaluate absolute changes in FVC (L and % predicted) measured with home spirometry, and oxygen saturation (%) measured with pulse oximetry, from baseline to 6, 12, and 24 months. These changes will be analyzed using a linear mixed model with disease and country as fixed effects. Repeated measurements within a patient will be corrected by random effects (intercepts or slopes, depending on the data). This model corrects for random missing data. Possible non-linear evolutions and correlations between subsequent observations will be accounted for through flexible modeling of the time variable and structured error terms in the variance–covariance matrix of the random effects. Absolute in-hospital FVC changes between baseline, 6, 12 and 24 months (L and %predicted), HRQOL, and symptom scores will also be assessed with linear mixed models. The correlation of home and hospital spirometry will be analyzed by calculating Pearson’s correlation coefficient, taking the individual mean FVC changes for each patient into account. Results will be used to optimize analytical methods to deal with outliers and missing data. Besides, a delta (Δ) change will be computed for HRQOL and symptom changes from baseline to 6, 12 and 24 months. Furthermore, we will use group based trajectory modeling and joint models to predict outcomes in individual patients (e.g. respiratory related and all cause hospitalizations, disease progression, and mortality) To measure time to decline in HRQOL, we will use the minimal clinically important difference (MCID) for all individual patient reported outcomes. Joint models will be used to assess time to reach the MCID. Adherence to the home monitoring program will be assessed by evaluating the completeness of data. The total number of measurements from each participant will be divided by the number of expected measurements, for pulmonary function as well as PROMs. The incidence rate of new oxygen prescription, non-elective hospitalization (respiratory and all cause), mortality (all cause and respiratory-related) will be summarized descriptively by diagnosis cohort. Disease progression will be defined according to the guideline criteria and its individual components, and will be compared with criteria used in different trials [16–18, 20]. We will also perform analyses with different cut-off values for FVC and DLCO. Multivariate logistic regression, ROC curve analysis and a multivariate Cox proportional hazards model will be used to identify possible predictive factors for disease progression and/or mortality. Differences between countries will be analyzed with ANOVA. If possible, HRQOL questionnaires will be validated for the different forms op PF by assessing internal consistency, discriminative ability, concurrent validity, and responsiveness. Patient and healthcare providers satisfaction with the home monitoring program will be summarized descriptively. An overview of the pre-specified endpoints is shown in Table 3.

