
**Table 3 Tab3:** Prespecified endpoints of the I-FILE study

*Primary endpoint*
Absolute FVC change measured with home spirometry from baseline to 6, 12 and 24 months (in % and L)
*Secondary endpoints*
Absolute FVC change measured with in-hospital spirometry between baseline and 6, 12 and 24 months (in % and L) Absolute DLCO change measured with in-hospital spirometry between baseline and 6, 12 and 24 months (in % and L) Change in oxygen saturation from baseline to 6, 12 and 24 months (in %) Correlations between home and hospital spirometry Adherence to daily and weekly home spirometry HRQOL and symptom changes between baseline, 6, 12 and 24 months Time to change in HRQOL Correlations between pulmonary function tests and PROMs at all time points Internal consistency, discriminative ability, concurrent validity, and responsiveness of PROMs in individual diseases Hospitalizations (all cause and respiratory related) Mortality Percentage of patients with disease progression Identification of markers for disease progression or death Percentage of patients with new oxygen prescription Differences in outcomes between countries Differences in outcomes between subgroups of PF Healthcare provider and patient satisfaction and experience with the online application

*FVC* Forced vital capacity, *HRQOL* Health related quality of life, *PROMs* Patient reported outcome measures, *PF* Pulmonary fibrosis

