During the last decade, many patient registries have been established for PF, with most registries focusing on IPF. Registry data are especially of added value for rare diseases with a heterogeneous disease trajectory, to gain more real-life insights in disease behavior and response to treatment. Compared to randomized controlled trials, registries have less strict inclusion criteria, as they operate more aligned with daily clinical practice. Therefore, registries include patients with a broader range of disease severity, who are often older, have more pulmonary function impairment, and more comorbidities. Moreover, larger patient groups can be included and monitored for a longer time period. However, registry data also have drawbacks. Combining data from different registries is hampered by factors such as data ownership, diverse patient populations, and differences in study parameters and outcomes. Due to the study design and less strict in- and exclusion criteria, registries often encounter more missing and heterogeneous data compared to clinical trials. In addition, patients with more severe disease can possibly have a higher dropout rate, whereas patients with a relatively mild disease course may be lost to follow up if they are referred to local centers for follow up. Until now, most PF registries are retrospective and often included patients from a single country. The I-FILE study provides solutions to overcome these hurdles. The eHealth technology used in this study facilitates uniform and frequent data collection from different countries across Europe. Since patients are tracking their disease course at home, they can provide data for a long period of time independent of their treating center. Data entry in traditional registries is mostly conducted by healthcare providers or research staff and is often very time consuming. In the I-FILE study, we chose to place patients in the lead by giving them ownership of their own study data. Patients collect data and give authorization for using their data for scientific research. We hypothesize that, compared to existing registry processes, patient-led data registration is less laborious for healthcare providers and research staff, and provides a more practicable way of frequent data logging at minimal burden for patients. The experience and satisfaction of all stake holders will be evaluated.

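### Logistic regression and ROC analysis, listed unranked beside a Cox model for predictors of progression or death, can be biased by severity-related loss and, for progression alone, by prior death

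*Protocol article*

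**What the plan says.** The section Endpoints and statistical analysis states: "Multivariate logistic regression, ROC curve analysis and a multivariate Cox proportional hazards model will be used to identify possible predictive factors". The outcome is given as "predictive factors for disease progression and/or mortality", so progression alone, death alone and a composite all remain possible. The three methods appear in one list with no order of importance. Table 3 carries the matching secondary endpoint, "Identification of markers for disease progression or death", and also lists the percentage of patients with disease progression.

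Four other statements bear on the point:

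- On the outcome: "Disease progression will be defined according to the guideline criteria and its individual components". No time window is attached to the binary version.
- On further models: "we will use group based trajectory modeling and joint models to predict outcomes in individual patients", with progression and mortality among the examples.
- On missing data: "This model corrects for random missing data". This refers to the linear mixed model for change in FVC and oxygen saturation, not to the logistic or ROC analyses.
- On follow-up, from the Abstract: "Patients will monitor their disease course for a period of two years".

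The Discussion says of registries in general that "patients with more severe disease can possibly have a higher dropout rate", and that patients with milder disease may be lost when referred to local centres.

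**The concern.** Progression and death accrue over two years of follow-up. Binary logistic regression and a standard ROC curve need a known yes or no for each patient over a fixed window. A patient who leaves before the end of that window without an event has no such status and must be coded event-free or dropped. A patient who dies before progressing raises the same question when progression alone is the outcome.

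If disease severity drives progression, death and dropout together, either choice distorts the apparent strength of severity-related markers, in opposite directions. The Background cites a median survival of two to three years in untreated IPF, so deaths within follow-up are plausible. Marker identification is a prespecified secondary endpoint. At stake is whether the reported odds ratios, AUCs and cut-offs describe the disease or a coding choice. A Cox model reported alongside does not repair them.

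**Working it through.** **The plan's own figure.** There is none to reproduce. The article gives no event rate, dropout rate, predictor effect or AUC, and the target of about 700 patients comes without a calculation. Every rate below is an assumption.

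**Model.** One standard-normal predictor *x*, 400,000 simulated patients per scenario, horizon 24 months. Times to progression, death and dropout are exponential with hazard λ·HR^x, and λ is set so that each event, taken alone, has the assumed 24-month risk. Progression is 40%, death 15% or 25%, dropout 0 to 30%. The hazard ratio per SD is 1.5 for progression, 2.0 for death, and 1.0 (unrelated) or 1.5 (related) for dropout. The reference is the same logistic model and AUC with full 24-month status.

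**Composite of progression or death (odds ratio / AUC)**

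| Death; dropout | Full status | Dropouts coded event-free | Dropouts excluded |
|---|---|---|---|
| 15%; none | 1.92 / 0.670 | 1.92 / 0.670 | 1.92 / 0.670 |
| 15%; 20% unrelated | 1.92 / 0.670 | 1.84 / 0.660 | 1.93 / 0.672 |
| 15%; 20% related | 1.93 / 0.670 | 1.69 / 0.641 | 2.03 / 0.681 |
| 25%; 30% unrelated | 2.09 / 0.688 | 1.92 / 0.669 | 2.11 / 0.691 |
| 25%; 30% related | 2.09 / 0.688 | 1.68 / 0.639 | 2.25 / 0.704 |

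AUC shifts with related dropout:

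- 20%: 0.641 − 0.670 = −0.029, or 0.681 − 0.670 = +0.011.
- 30%: 0.639 − 0.688 = −0.049, or 0.704 − 0.688 = +0.016.

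AUC shifts with unrelated dropout:

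- 20%: −0.010 or +0.002.
- 30%: −0.019 or +0.003.

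**Mortality.** With no dropout there is no bias (2.14 / 0.695 under every coding). With 15% death and 20% related dropout, the reference is 2.17 / 0.699, against 1.99 / 0.682 (coded event-free) or 2.30 / 0.710 (excluded).

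**Progression alone.** With no dropout and 15% death, the answer depends only on how deaths are handled:

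- Deaths counted as non-progressors: 1.51 / 0.614. This is correct for the real-world risk of progressing.
- Deaths excluded: 1.82 / 0.655.
- Hypothetical world without death: 1.70 / 0.642.

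With 25% death and 30% related dropout, the real-world reference is 1.39 / 0.593. Counting all leavers as non-progressors gives 1.28 / 0.571, and excluding them gives 2.06 / 0.680.

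**Percentage with progression.** Constant hazards without a predictor are enough here. Over 24 months the cumulative hazards are:

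- progression: −ln 0.60 = 0.511
- death: −ln 0.85 = 0.163
- dropout at 20%: −ln 0.80 = 0.223

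Then:

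- True cumulative incidence: 0.511/(0.511 + 0.163) × (1 − 0.60 × 0.85) = 0.759 × 0.490 = 37.2%.
- Progression observed before death or dropout: 0.511/0.896 × (1 − 0.60 × 0.85 × 0.80) = 0.570 × 0.592 = 33.7%. This is the result if leavers count as non-progressors.
- Leavers excluded: 0.337/(0.337 + 0.408) = 45.3%.

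So a simple proportion would read 34% or 45% for a true 37%. Unlike the predictor effects, it moves appreciably even when dropout is unrelated to severity.

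**The case against.** A reader might infer that the plan as a whole ignores censoring. It does not: the quoted sentence names a Cox model, and the same section plans joint models for progression and mortality. That limits the concern to the logistic, ROC and simple-proportion outputs.

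A reader might also take the outcome to be two-year status analysed with an ordinary ROC curve. The article states neither a horizon nor a type of ROC, and a time-dependent ROC is not excluded.

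Nor does the Discussion forecast differential dropout for this study. It describes registries in general, then presents home monitoring as a remedy because patients can supply data independently of their centre. Six-monthly outpatient visits, reminders for missed measurements and separately requested access to records for five further years also help. This stands in part. Guideline progression combines symptoms with radiological or physiological change, and DLCO is measured in hospital, so a patient who leaves the centre may still have unknown progression status.

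Death before progression is no problem for mortality or for the composite. For progression alone, the odds ratio of 1.70 belongs to a world without death, so measuring bias against it would mix a change of estimand with an error. Nor is a numerical gap between odds ratio and hazard ratio evidence of a defect: with complete follow-up and no death, a hazard ratio of 1.5 already corresponds to an odds ratio of 1.70.

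Finally, this is an exploratory secondary analysis in a condensed article. The horizon and the coding of leavers may be set out in the full protocol or an analysis plan, so their absence here is not the point. The choice of methods, with none given precedence, is stated here.

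**Conclusion.** The concern holds in conditional form. Logistic regression and a standard ROC curve can misstate predictor effects and discrimination if loss depends on severity, or if deaths precede progression and progression alone is the outcome. The direction depends on coding: on the assumed rates, coding dropouts event-free pulls the composite odds ratio and AUC down, and excluding them pushes both up. The percentage with progression is exposed in the same way if computed as a simple proportion.

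The size cannot be established from the article. On the assumed rates, the composite AUC shifts by about 0.01 to 0.05 with 20-30% predictor-related dropout and by about 0.01 or less with 20% unrelated dropout. There is no bias for mortality or the composite with complete status. The documents do not support saying that these analyses will be biased, only that they can be. This is a worthwhile improvement to a secondary analysis and leaves the primary FVC endpoint untouched.

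**What to change.** Name the Cox model as the main analysis of predictors: cause-specific for progression, with death as a competing event, and the usual form for mortality or the composite. Replace the ROC analysis by time-dependent ROC at stated horizons, for example 12 and 24 months, with inverse-probability-of-censoring weights. Report the percentage with progression as an Aalen-Johansen cumulative incidence with death as the competing event. If a logistic model is kept, label it supportive and give its horizon and its rule for leavers and deaths.

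The Cox model and the weights still assume that dropout is explained by the covariates in them, so baseline severity should be included in both.

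The cost is a change of wording and slightly more programming in standard software. No new data are needed.

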### Study design and participants

The I-FILE study is an ongoing prospective multicenter, multinational, observational pilot study (NCT04304898). Patients with ILD, newly diagnosed in a multidisciplinary discussion (MDD), and PF on high-resolution computed tomography (HRCT), will be included in both community and tertiary centers in Belgium, France, Germany, Greece, the Netherlands, Norway and The United Kingdom. The trial is currently underway, and patients are being recruited. We aim to include approximately 700 patients in total. Patients will be considered newly diagnosed, when the diagnosis has been established within six months before inclusion in an MDD. In addition, patients should be either treatment naïve or have received treatment for their PF for a maximum of one month before inclusion. For more detail, inclusion—and exclusion criteria are shown in Table 1.

**Table 1 Tab1:** Inclusion and exclusion criteria of the I-FILE study

Inclusion criteria	Exclusion criteria
Newly diagnosed patients with ILD and PF on HRCT Pulmonary fibrosis present on HRCT according to current guidelines, confirmed by a thoracic radiologist at the MDD [20] MDD diagnosis ≤ 6 months before inclusion Treatment for ILD ≤ than 1 month	Not able to speak, read or write in the native language of the country where the patient is included
	Not able to comply to the study protocol, according to the judgement of the investigator and/or patient
	No access to the internet

*ILD* Interstitial lung disease*, PF* Pulmonary fibrosis*, MDD* Multi-disciplinary discussion*, HRCT* High-resolution computed tomography

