Results of this study will provide insights into disease behavior across different forms of PF. Because of the sample size and duration, we expect to be able to evaluate relatively large subgroups of individual diseases and rare events, such as acute exacerbations. Frequent home spirometry measurements may facilitate early detection of acute exacerbations and disease progression. This is particularly relevant in this patient population, since there is a paucity of prognostic and predictive biomarkers. Data from this study can shed light on whether the use of home spirometry can optimize timing of treatment initiation for individual patients. The I-FILE study will also reveal potential differences in clinical management and outcomes of patients with PF across different European countries.

Earlier studies have elucidated the potential benefits of online home monitoring for patients with PF, both for regular care and research purposes. A randomized controlled trial in IPF found that an online home monitoring program, including home spirometry and online completion of patient-reported outcome measures, tended to improve psychological wellbeing compared to standard care, and was highly appreciated by patients. In addition, online home monitoring allowed for early treatment adjustments in individual patients in case of pulmonary function decline or side-effects of treatment [22]. Results of the I-FILE will build on these insights and show whether home monitoring of patients with potentially progressive disease remains viable and beneficial on the long-term. We postulate that real-time access to pulmonary function, symptoms, and HRQOL data can enhance patient engagement and self-management, as patients gain more insights in their own disease course. The I-FILE study will also reveal whether disease course has influence on the adherence to home monitoring. For research purposes, frequent online data collection using home monitoring can facilitate early identification of patients with a progressive phenotype for inclusion in clinical trials, as well as possibilities for real-time safety monitoring, and broader access to trials [21].

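### ANOVA is named for country differences beside a mixed model that already holds disease and country; the two routes are not reconciled, and the ANOVA route states no adjustment for diagnosis mix

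*Protocol article*

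**What the plan says.** All statements are in the protocol article.

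- Endpoints and statistical analysis gives the method for country comparisons in one sentence: "Differences between countries will be analyzed with ANOVA". It names no factors, covariates or outcomes.
- Table 3 lists the matching secondary endpoint as "Differences in outcomes between countries". The other secondary endpoints there include mortality, hospitalizations, the percentage with progression, the percentage with new oxygen prescription, and time to change in HRQOL.
- For home FVC and oxygen saturation the same section says: "These changes will be analyzed using a linear mixed model with disease and country as fixed effects". It adds random effects for repeated measurements within a patient and states: "This model corrects for random missing data".
- For in-hospital FVC and the patient-reported scores, "HRQOL, and symptom scores will also be assessed with linear mixed models", without restating the fixed effects.
- New oxygen prescription, non-elective hospitalization and mortality are to be summarized descriptively by diagnosis cohort. Logistic and Cox models are named for finding predictors of progression or mortality, not for comparing countries.
- Study design and participants says that patients from seven countries "will be included in both community and tertiary centers".
- The Discussion expects the study to "reveal potential differences in clinical management and outcomes of patients with PF across different European countries".

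**The concern.** The mixed model puts disease beside country, which is what a country comparison needs when outcome depends on diagnosis. The Background says that disease course varies with etiology. The sentence written for the country comparison does not mention disease. A reader cannot tell whether the country endpoint will be answered by the mixed model's country term, by a separate ANOVA, or by both, nor which would prevail if they disagreed.

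If the ANOVA is run without disease, a country that enrols more patients with a faster-declining diagnosis will show a larger mean loss of FVC even if patients with the same diagnosis fare alike everywhere. Recruitment through community and tertiary centres in seven countries makes unequal case mix plausible. A separate ANOVA would also not carry the mixed model's handling of repeated measurements and random missing data. Since the Discussion means to interpret country differences, a case-mix difference could be reported as a difference in outcome between countries.

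**Working it through.** **Two routes to a country effect**

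| | Mixed model | ANOVA sentence |
|---|---|---|
| Outcomes | Home FVC and oxygen saturation change | Not specified; the endpoint says outcomes in general |
| Country in the model | Yes, fixed effect | Yes |
| Disease in the model | Yes, fixed effect | Not stated |
| Repeated measurements | Random effects | Not stated |
| Missing data | Said to correct for random missingness | Not stated |

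No sentence links the two columns. This part needs no assumption.

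**Size of the possible case-mix effect**

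The article gives no SD, country sizes, diagnosis shares or alpha for this comparison, so there is no figure to reproduce. The approximate total of 700 patients and the seven countries come from the article. Everything else is assumed: equal split (100 per country), SD 350 mL within diagnosis, IPF declining d = 100 or 200 mL more than other diagnoses, IPF share p rising in equal steps across countries, no true country effect, two-sided 5% test.

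1. Largest spurious difference between two countries = (highest share − lowest share) × d. For shares of 20% to 80% and d = 200: 0.6 × 200 = 120 mL.
2. Variance within a country, averaged = 350² + d² × mean of p(1 − p).
3. Noncentrality of the one-way F test: λ = 100 × d² × Σ(p − mean p)² / variance, on 6 and 693 degrees of freedom (5% critical value 2.11).
4. Example, shares 20% to 80%, d = 200: Σ(p − 0.5)² = 0.28; mean p(1 − p) = 0.21; variance = 122,500 + 40,000 × 0.21 = 130,900; λ = 100 × 40,000 × 0.28 / 130,900 = 8.56; rejection probability 0.56.

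| IPF share across countries | Spurious difference, d = 100 / 200 mL | λ | Rejection (noncentral F) | Rejection (2,000 simulated data sets each) |
|---|---|---|---|---|
| 40% to 60% | 20 / 40 mL | 0.25 / 0.94 | 6.0% / 9.0% | 6.5% / 9.9% |
| 30% to 70% | 40 / 80 mL | 1.00 / 3.78 | 9.3% / 25.3% | 10.0% / 24.9% |
| 20% to 80% | 60 / 120 mL | 2.25 / 8.56 | 15.9% / 55.9% | 15.2% / 55.4% |

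**Check that adding disease removes the effect**

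A separate simulation used other assumed inputs: SD 250 mL, disease difference 50, 100 or 150 mL, 7 × 100 patients, 4,000 runs per scenario.

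| Share of the faster-declining disease | One-way ANOVA, 50 / 100 / 150 mL |
|---|---|
| 40% everywhere | 5.5% / 4.5% / 5.4% |
| 30% to 50% | 5.3% / 7.4% / 9.8% |
| 20% to 60% | 6.9% / 14.4% / 28.9% |
| 10% to 70% | 9.8% / 29.1% / 60.8% |

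With disease in the model, rejection for country was 4.4% to 5.6% in every scenario. The inflation comes from unequal case mix alone, is absent when case mix is equal, and goes when disease is included.

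These figures cover confounding by diagnosis only. Dropout, repeated measurements and event outcomes were not quantified.

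**The case against.** The strongest reply is that the article says only ANOVA. It does not say one-way, unadjusted or limited to patients with a value at a given visit. Factors and covariates are details that an article may leave to the full protocol or the analysis plan, and the sentence could even mean F tests on the mixed model's country term. This stands in part: a reader might infer that the plan compares unadjusted country means, but the text does not establish it. What remains is what the article itself fixes: a second method for a quantity already in the mixed model, with no link between them.

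A reader might also infer that the plan as a whole ignores case mix, repeated measurements and dropout. That is not so. For home FVC, the primary endpoint, and for oxygen saturation, the mixed model already gives a country term adjusted for disease and states how repeated measurements and random missingness are handled. The criticism applies to the ANOVA route only.

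Nor does the article say that mortality, hospitalization or oxygen prescription will be tested by ANOVA. These are planned descriptively by diagnosis cohort, and only the general word outcomes in Table 3 suggests otherwise. ANOVA is also an ordinary choice for a simple per-patient measure such as adherence.

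Finally, the size rests wholly on assumed inputs, and the upper figure needs IPF shares from 20% to 80%. Adjusting for centre type or baseline severity is debatable too, since it may remove part of the differences in care that the Discussion wants to describe. Both points stand, and they limit the conclusion and the fix.

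**Conclusion.** The point holds as an unreconciled choice of method for a secondary endpoint. The article names ANOVA for country differences, states no adjustment for diagnosis in it, and does not relate it to the mixed model that already contains disease and country. ANOVA would also be unsuitable for the binary and time-to-event outcomes in Table 3 if used for them.

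The bias is a conditional risk. Under the first set of assumptions, false rejection runs from about 6-10% under modest imbalance in IPF share to about 15-55% under strong imbalance, against a nominal 5%. The documents do not support saying that false country effects will occur, because they give no diagnosis mix by country. The primary endpoint's own model is not affected. The study is an observational pilot and the article attaches no decision rule to this comparison, so the weight is moderate. The correction is worth making because the better model is already in the plan.

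**What to change.** Replace the ANOVA sentence with text to this effect:

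- Country differences in FVC, DLCO, oxygen saturation and patient-reported outcomes are estimated as country contrasts from the linear mixed model with disease as a fixed effect. If the modelled outcome is the level over time rather than the change, use country-by-time contrasts and include disease by time, so that rates of change are also adjusted for diagnosis.
- Any country comparison of events uses logistic or Cox models, as the outcome requires, adjusted for disease. If events are only to be described, say so and exclude them from the country endpoint.
- Further adjustment for age, sex, baseline lung function and centre type is a sensitivity analysis, with a note that it may remove part of the differences in care between countries.
- ANOVA may stay for simple per-patient measures such as adherence, with those measures named.

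The cost is analysis work and a short text change. Demographics, clinical characteristics and hospital lung function are collected at inclusion according to Study procedures. Centre type is not listed there and would need to be recorded once per centre for the sensitivity analysis.
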